# Stress ulcer prophylaxis versus placebo—a blinded randomized control trial to evaluate the safety of two strategies in critically ill infants with congenital heart disease (SUPPRESS-CHD)

**DOI:** 10.1186/s13063-020-04513-w

**Published:** 2020-06-29

**Keywords:** Pediatric critical care, Pediatric cardiac critical care, Pediatric intensive care, H2 blocker, Congenital heart disease, Gastrointestinal hemorrhage, Infection, Microbiome

## Abstract

**Background:**

Critically ill infants with congenital heart disease (CHD) are often prescribed stress ulcer prophylaxis (SUP) to prevent upper gastrointestinal bleeding, despite the low incidence of stress ulcers and limited data on the safety and efficacy of SUP in infants. Recently, SUP has been associated with an increased incidence of hospital-acquired infections, community-acquired pneumonia, and necrotizing enterocolitis. The objective of this pilot study is to investigate the feasibility of performing a randomized controlled trial to assess the safety and efficacy of withholding SUP in infants with congenital heart disease admitted to the cardiac intensive care unit.

**Methods:**

A single center, prospective, double-blinded, randomized placebo-controlled pilot feasibility trial will be performed in infants with CHD admitted to the cardiac intensive care unit and anticipated to require respiratory support for > 24 h. Patients will be randomized to receive a histamine-2 receptor antagonist (H2RA) or placebo until they are discontinued from respiratory support. Randomization will be performed within 2 strata defined by admission type (medical or surgical) and age (neonate, age < 30 days, or infant, 1 month to 1 year). Allocation will be a 1:1 ratio using permuted blocks to ensure balanced allocations across the two treatment groups within each stratum. The primary outcomes include feasibility of screening, consent, timely allocation of study drug, and protocol adherence. The primary safety outcome is the rate of clinically significant upper gastrointestinal bleeding. The secondary outcomes are the difference in the relative and absolute abundance of the gut microbiota and functional microbial profiles between the two study groups. We plan to enroll 100 patients in this pilot study.

**Discussion:**

Routine use of SUP to prevent upper gastrointestinal bleeding in infants is controversial due to a low incidence of bleeding events and concern for adverse effects. The role of SUP in infants with CHD has not been examined, and there is equipoise on the risks and benefits of withholding this therapy. In addition, this therapy has been discontinued in other neonatal populations due to the concern for hospital-acquired infections and necrotizing enterocolitis. Furthermore, exploring changes to the microbiome after exposure to SUP may highlight the mechanisms by which SUP impacts potential microbial dysbiosis of the gut and its association with hospital-acquired infections. Assessment of the feasibility of a trial of withholding SUP in critically ill infants with CHD will facilitate planning of a larger multicenter trial of safety and efficacy of SUP in this vulnerable population.

**Trial registration:**

ClinicalTrials.gov, NCT03667703. Registered 12 September 2018, https://clinicaltrials.gov/ct2/show/NCT03667703?term=SUPPRESS+CHD&draw=2&rank=1.

All WHO Trial Registration Data Set Criteria are met in this manuscript.

## Background

Stress ulcer prophylaxis (SUP) is prescribed in the critically ill to decrease the incidence of stress-related mucosal damage that can lead to upper gastrointestinal (UGI) bleeding. The development of an UGI bleed while critically ill has been associated with increased intensive care unit (ICU) length of stay and mortality [1]. The adult practice of SUP administration has subsequently been adopted in neonatal and pediatric ICUs. However, the incidence of clinically significant UGI bleeds is very low, and there are limited data on the efficacy of SUP in critically ill infants and children [2]. Furthermore, the safety and efficacy of SUP has been called into question even in adults over the last decade [3–8].

In both adults and children, the incidence of clinically significant UGI bleeding is declining and hypothesized to be related to earlier initiation of enteral nutrition and increased utilization of goal-directed therapies [9]. Therefore, focus has shifted away from the utility of SUP and onto the safety and potential benefits of withholding this therapy. In critically ill adults, SUP has been associated with ventilator-associated pneumonia and *Clostridioides difficile* colitis [10, 11]. Similarly, in a large multicenter cohort, we reported a significant association between SUP and ventilator-associated pneumonia in critically ill children [8]. Several publications have also described an increase in bacteremia, necrotizing enterocolitis, and mortality in the neonatal ICU when patients were exposed to SUP [3, 5, 6]. These earlier studies have been limited by observational study design and potential confounding by indication. A definitive trial comparing administration versus withholding of SUP in critically ill infants with CHD is lacking. Based on the findings of prior studies, the role of SUP is being questioned [4, 12]. Furthermore, recent advances in molecular methods have allowed a shift from traditional culture-based techniques to detect gut microbiota to high-throughput DNA sequencing methods. The impact of acid suppression on the gut microbiota, especially the change in proportion of unfavorable organisms such as *C. difficile* and/or aerobic Gram-negative bacilli, may be an important mechanistic link between SUP and increased risk of infections.

Critically ill infants with congenital heart disease (CHD) are at risk for stress-related mucosal damage due to reduced splanchnic blood flow leading to mucosal ischemia and reperfusion injury, yet there is currently no consensus among pediatric cardiac intensivists regarding the clinical indications for SUP [13]. Therefore, the central objective of our study is to investigate the feasibility of conducting a clinical trial to assess the safety of withholding SUP in infants with CHD in the cardiac intensive care unit. Our hypothesis is that this trial design is feasible. We will also examine serial changes in the gut microbiota as a secondary aim to examine the difference in microbial profiles of patients receiving acid suppressive therapy compared to those receiving placebo. Our hypothesis is that patients receiving SUP will have decreased abundance and heterogeneity of gastrointestinal microbiota. Results of this feasibility trial will allow us to further refine inclusion and exclusion criteria, study procedures, data acquisition strategy, and study outcomes for a future multicenter, randomized controlled trial.

## Methods

### Study design

The study is a prospective, double-blinded randomized placebo-controlled pilot feasibility trial in a pediatric cardiac ICU at Boston Children’s Hospital, a quaternary freestanding children’s hospital. Enrollment began in February 2019 with a planned enrollment of 100 patients over a 2-year period. The local Institutional Review Board (IRB) at Boston Children’s Hospital approved this study. All study protocol amendments, deviations, or adverse events will be immediately reported to IRB. All research team members, clinicians, data analysts, and trial participants are blinded to study assignments. Unblinding will only occur in the event a participant has a serious adverse event such a clinically significant gastrointestinal bleed. The study was registered at ClinicalTrials.gov (NCT03667703) and funded by The Gerber Foundation’s National Research Grant (#5781). The funding agency will have no access to or involvement in the data analysis or writing of the manuscripts. The research integrity, data quality, and adverse event assessment will be regularly reviewed by a pre-appointed, independent Data Safety Monitoring Board (DSMB). The DSMB has an appointed chair and five other members. Further details regarding the charter can be available by contacting the corresponding author who is a co-principal investigator. Table 1 shows the Standard Protocol Items: Recommendation for Interventional Trials (SPIRIT) schedule for the enrollment, intervention, and assessment periods. The SPIRIT checklist is in Additional file 1.

**Table 1 Tab1:** Standard Protocol Items: Recommendation for Interventional Trials (SPIRIT) schedule of enrollment, interventions, and assessments

Time point			Study period			
		Enrollment	Allocation		Post-allocation	Close-out
		Pre-study	Study day #1	Study day #2 through up to 14	24 h after respiratory support discontinued	Hospital discharge
Enrollment	Eligibility screen	**♦**	**♦**			
	Informed consent	**♦**	**♦**			
	Allocation		**♦**			
Intervention	H2 blocker or placebo		**♦**	**♦**		
Assessments	Demographics		**♦**	**♦**	**♦**	
	Laboratory data		**♦**	**♦**	**♦**	
	Antibiotic exposure		**♦**	**♦**	**♦**	
	Inotrope and vasoactive use		**♦**	**♦**	**♦**	
	Nutritional support		**♦**	**♦**	**♦**	
	Gastrointestinal bleeding		**♦**	**♦**	**♦**	**♦**
	Necrotizing enterocolitis		**♦**	**♦**	**♦**	**♦**
	Infectious complications		**♦**	**♦**	**♦**	**♦**
	Adverse event		**♦**	**♦**	**♦**	**♦**
	Oral, gastric, blood, and urine samples		**♦**		**♦**	**♦**
	Stool samples		**♦**	**♦**	**♦**	**♦**
	Length of stay					**♦**
	Mortality					**♦**

### Study population

The inclusion and exclusion criteria are described in Table 2. Infants diagnosed with CHD admitted to the cardiac ICU and anticipated to require respiratory support (defined below) for greater than 24 h will be eligible for the study. Congenital heart disease includes anatomic, myopathic, and arrhythmic conditions. Respiratory support is defined as mechanical ventilation, including conventional, high frequency oscillatory, or jet ventilation, as well as non-invasive positive pressure ventilation, such as continuous (CPAP) and biphasic (BIPAP) positive airway pressure, and high-flow nasal cannula. Respiratory support for greater than 24 h was chosen as a surrogate for severity of illness. Patients will be excluded if they receive any form of antacid for > 7 days during the past month as this could potentially alter their baseline gut microbiome. Patients will also be excluded if they are anticipated to receive high-dose steroids, intravenous non-steroidal anti-inflammatory agents, or high-dose aspirin during their hospitalization, as these medications may potentially cause gastritis and increase the risk for UGI bleeding. Finally, infants on certain anticoagulants—direct thrombin inhibitors and GPIIbIIIa inhibitors—will be excluded since these medications do not have an available reversal agent in the event of an UGI bleed.

**Table 2 Tab2:** Eligibility criteria

**Inclusion criteria**	(1) < 12 months of age (including premature newborns) (2) Diagnosed with congenital heart disease* (3) Admitted to the CICU (4) Anticipated to require respiratory support^¶^ for > 24 h during their CICU stay (5) Have received ≤ 1 dose of stress ulcer prophylaxis^β^ during their current admission
**Exclusion criteria**	(1) Prior use of antacids^β^ in the past month for > 7 days (2) Active gastrointestinal bleeding (3) Active *Helicobacter pylori* infection (4) Anticipated exposure to certain pharmaceuticals: (i) High-dose steroids (equivalent to 4 mg/kg/day of methylprednisolone) (ii) Intravenous non-steroidal anti-inflammatory drugs (i.e., ketorolac) (iii) Certain anticoagulants including high-dose aspirin, direct thrombin inhibitors, and GPIIbIIIa inhibitors (5) Planned to undergo or recently has undergone gastrointestinal surgery within the last 4 weeks (6) Supported by ECMO or VAD (7) Currently enrolled in another conflicting interventional trial (8) Known to be allergic to H2RAs (9) Admitted for palliative care (10) Prior enrollment in the study (11) Primary provider declines enrollment

*CICU* cardiac intensive care unit, *H2RA* histamine-2 receptor antagonist, *PPI* proton pump inhibitor, *GIIbIIIa* glycoprotein IIb/IIIa, *ECMO* extracorporeal membrane oxygenator, *VAD* ventricular assist device

*CHD includes anatomic, myopathic, and arrhythmic conditions

^¶^Respiratory support includes mechanical ventilation, non-invasive positive pressure ventilation, and high-flow oxygen therapy

^β^Stress ulcer prophylaxis or antacids include H2RAs, PPIs, and sucralfate

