### Study intervention

Study participants will be randomly assigned to receive a histamine-2 receptor antagonist (i.e., ranitidine or famotidine) or placebo. As there are no pediatric-specific recommendations regarding type of SUP, we elected to conduct our study with a histamine-2 receptor antagonist since this is the current standard practice at our institution. In this pragmatic design, participants can receive study drug either intravenously or enterally, depending on the clinician’s preference. The dosing is based on age and route. For ranitidine, neonates (< 31 days old) will receive either 1 mg/kg intravenously/enterally every 12 h, and infants (≥ 31 days old) will receive 1 mg/kg intravenously/enterally every 8 h. For famotidine, if the participant is < 3 months, they will receive 0.5 mg/kg/dose IV/PO daily, and if > 3 months old, they will receive 0.25 mg/kg/dose IV every 12 h or 0.5 mg/kg/dose PO every 12 h. As part of pharmacovigilance, surveillance for hepatic dysfunction and thrombocytopenia will be included in the case report forms.

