### Outcomes

The central objective for our pilot study is to investigate whether a clinical trial assessing the safety and efficacy of withholding SUP in infants with CHD in the cardiac ICU is feasible. The trial will be considered feasible if each of the following 4 a priori variables are met: (1) > 80% of eligible patients are approached for consent (*screening*), (2) > 20% of eligible patients are randomized (*enrollment and consent*), (3) > 80% of consented patients received their first dose of study drug within 48 h (*allocation*), and (4) > 80% protocol compliance achieved (*protocol adherence*). Adherence to the protocol is defined as having received all doses of study drug as prescribed during the study period. Protocol deviation is defined as either premature termination of the study or prescription of SUP that is not part of the study while enrolled. In addition to feasibility, we will assess safety by comparing the difference in the incidence of clinically significant UGI bleeding and hospital-acquired infections between participants receiving SUP versus placebo. Finally, we will explore the changes to the gut microbiota by comparing the absolute and serial differences in the abundance of bacteria and functional microbial profiles between those receiving SUP compared to placebo. The study investigators will not be blinded to primary outcome measures. The microbiome specimens (for secondary outcome measure) will be processed and analyzed without revealing their study group allocation and thus will be blinded.

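### Provider refusal is an exclusion criterion, so it drops out of the denominators of feasibility criteria 1 and 2 and the feasibility decision cannot register it

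*Protocol article*

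**What the plan says.** Under Study population, the protocol article states: "The inclusion and exclusion criteria are described in Table 2". That table is titled as the eligibility criteria, and its last exclusion is "11) Primary provider declines enrollment". Recruitment and study flow says that an investigator approaches the family of an eligible patient.

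Outcomes sets the decision rule: "The trial will be considered feasible if each of the following 4 a priori variables are met". Criterion 1 is "> 80% of eligible patients are approached for consent" and criterion 2 is "> 20% of eligible patients are randomized". Criterion 3 starts after consent ("> 80% of consented patients received their first dose of study drug within 48 h"), and criterion 4 concerns compliance once on study.

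Two other places touch the point. Sample size words the screening target as 80% of all patients, with n = 600. Study intervention halts the study for DSMB review if fewer than 20 patients are enrolled per year.

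**The concern.** A provider's refusal is not a characteristic of the infant. It is a barrier to recruitment, and a foreseeable one here. The Background says "there is currently no consensus among pediatric cardiac intensivists regarding the clinical indications for SUP", and Study intervention explains that an H2 blocker was chosen "since this is the current standard practice at our institution". Some clinicians may be unwilling to risk placebo for a given infant, and a pilot should measure how often.

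The protocol treats the same clinical judgement differently according to when it is made. After enrollment, a provider's wish for open-label acid suppression ends study procedures, and premature termination or non-study prophylaxis counts as a protocol deviation. Before enrollment, the refusal makes the infant ineligible and none of the four criteria sees it. A positive feasibility verdict is meant to lead to a multicenter non-inferiority trial, so approach and randomization rates that leave out this barrier could mislead its planning.

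**Working it through.** **The protocol's own figures.** Sample size gives 82.7% (n = 600) and 86.9% (n = 100) as the observed rates at which a one-sided 95% lower limit reaches 80%. Solving the exact (Clopper-Pearson) limit for a continuous count gives 82.74% and 86.89%, so both reproduce. This point does not dispute them. It concerns who is counted in the denominator.

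**Inputs.**
- E = 200 infants who meet every criterion other than provider agreement. This is an assumption, anchored to the 200 eligible patients expected over two years under Sample size.
- r = share of E whose provider declines. The protocol gives no rate; 10, 20, 30 and 50% are assumed.
- Thresholds of 80% and 20%, from Outcomes.

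**Denominators.** As written, criteria 1 and 2 use E(1 − r). With refusals retained, they use E.

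**Smallest number approached that passes criterion 1.** The bare rule needs a count above 0.80 × E(1 − r). The stricter reading requires the exact one-sided 95% lower limit to reach 80%.

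| r | E(1 − r) | Bare rule: count | as % of 200 | Exact limit: count | as % of 200 |
|---|---|---|---|---|---|
| 10% | 180 | 145 | 72.5 | 154 | 77.0 |
| 20% | 160 | 129 | 64.5 | 137 | 68.5 |
| 30% | 140 | 113 | 56.5 | 121 | 60.5 |
| 50% | 100 | 81 | 40.5 | 87 | 43.5 |

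On either reading, criterion 1 passes although fewer than 80% of the otherwise-eligible infants were approached.

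**Where criterion 1 reverses.** If a share a of the non-refused infants is approached, the share of all otherwise-eligible infants is a(1 − r). It falls below 0.80 when r > 1 − 0.80/a.
- a = 0.90: r > 1 − 0.80/0.90 = 11.1%.
- a = 0.95: r > 1 − 0.80/0.95 = 15.8%.

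**A worked case for both criteria.** Assume 90% of non-refused infants are approached and 50% of those are randomized, so 0.90 × 0.50 = 45% of the non-refused are randomized.

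| r | Criterion 1 / 2 as written | Criterion 1 / 2 with refusals retained | Randomized per year |
|---|---|---|---|
| 0% | 90% / 45% | 90.0% / 45.0% | 45.0 |
| 10% | 90% / 45% | 81.0% / 40.5% | 40.5 |
| 20% | 90% / 45% | 72.0% / 36.0% | 36.0 |
| 50% | 90% / 45% | 45.0% / 22.5% | 22.5 |
| 60% | 90% / 45% | 36.0% / 18.0% | 18.0 |

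As written, the rates are the same in every row. With refusals retained, criterion 1 fails above about 11% refusal and criterion 2 only above 1 − 0.20/0.45 = 55.6%.

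**The halting rule in the same case.** Twenty per year is 40 over two years. Randomized numbers fall below that when 200(1 − r) × 0.45 < 40, that is, r > 55.6%. If every non-refused infant were randomized, the point would be r > 1 − 40/200 = 80%.

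**The case against.** **The halting rule limits the damage.** This stands in part. The smallest counts that pass criterion 2 at 10, 20, 30 and 50% refusal are 37, 33, 29 and 21 over two years, or 18.5, 16.5, 14.5 and 10.5 per year. All are below 20, so each would trigger a halt unless infants enrolled but not randomized brought the total to 40. A reader might infer that the trial could be declared feasible however often clinicians refuse it. The four criteria taken alone allow that, but the protocol as a whole does not support it, because very frequent refusal would stop the study for review. The halt is still not a feasibility criterion, and in the worked case it acts only above about 56% refusal, far beyond the 11% at which criterion 1 reverses.

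**Refusals do not inflate the rates.** A reader might also infer that each refusal pushes the observed rates up. It does not: in the worked case they stay at 90% and 45% throughout. They are insensitive to refusal, and too high only as estimates for all otherwise-eligible infants.

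**The protocol uses the word eligible loosely.** The Study population text describes eligible infants without mentioning provider agreement, Recruitment speaks of mailers to eligible patients before delivery or surgery, and Sample size refers to all patients. These uses are real, but they do not override Outcomes, which states the operative rule, or Table 2, which says who is eligible. The difference between Sample size and Outcomes needs reconciling in its own right.

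**Refusals may be logged anyway.** They may be; nothing suggests they go unrecorded, and the Discussion expects the pilot to identify barriers. But a log entry does not enter the decision rule. That rule is fixed in the text shown, so this is not detail left to a fuller document.

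**Conclusion.** The concern holds in a limited form. Followed as written, Table 2 and Outcomes remove provider-declined infants from the denominators of criteria 1 and 2. The feasibility decision is then insensitive to provider refusal, and the two rates overstate approach and randomization among otherwise-eligible infants.

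The effect that matters is on criterion 1, where modest refusal is enough to reverse the result: about 11% if 90% of non-refused infants are approached, about 16% if 95% are. Criterion 2 has wide slack. The plan of 100 randomized from an expected 200 eligible is 50% against a threshold of 20%.

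The direction follows from the text alone. The sizes rest on assumed refusal, approach and consent rates and on taking 200 as the number before refusals. If the 200 is already net of refusals, the counts change but the reversal points do not. This should be corrected, but it does not show that the trial would in fact be wrongly declared feasible.

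**What to change.** Keep the provider's right to decline; no clinical rule changes, and item 11 need not be deleted. In Outcomes:

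1. Define the denominators of criteria 1 and 2 as infants meeting all Table 2 criteria other than provider agreement.
2. Count provider-declined infants as not approached and not randomized.
3. Report the provider-decline proportion with a one-sided 95% limit, in line with the Feasibility analysis section.
4. Reconcile the screening denominator under Sample size (all patients, n = 600) with the one under Outcomes (eligible patients), so that criterion 1 has a single definition.

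The cost is a sentence or two of text and a reason code in the screening log. The downside is that the observed feasibility rates become less favourable if refusals are common, and criterion 1 could then fail.

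### Provider refusal is an exclusion criterion, so refused infants leave the denominators of the approach and enrollment feasibility criteria; the approach criterion can pass when it should fail

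*Protocol article*

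**What the plan says.** Study population, Table 2, gives as the last of eleven exclusion criteria "Primary provider declines enrollment". Recruitment and study flow sets the order of events: patients are screened for eligibility, and the family of an eligible patient is then approached.

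Outcomes defines four feasibility criteria. The first requires that more than "80% of eligible patients are approached for consent", the second that more than "20% of eligible patients are randomized". All four must hold: "The trial will be considered feasible if each of the following 4 a priori variables are met".

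Feasibility analysis says that each proportion will be reported with a one-sided 95% confidence interval. Neither section says that provider refusals stay in a denominator or are counted separately.

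Two other places bear on the point. Inclusion criterion 5 in Table 2 allows at most one dose of stress ulcer prophylaxis (SUP) in the current admission. Study intervention explains the choice of an H2 blocker "since this is the current standard practice at our institution".

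**The concern.** Feasibility is the primary outcome of this pilot, and the Discussion makes the planned multicenter trial depend on it. The Background notes that pediatric cardiac intensivists have no consensus on when SUP is indicated. Unwillingness of the treating provider to have an infant randomized is therefore a foreseeable barrier, and one that a pilot should measure.

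The two definitions together prevent that. A refusal makes the infant ineligible, so it lowers neither the approach rate nor the enrollment rate. The more often providers refuse, the further both reported rates rise above what a later trial would meet among clinically suitable infants. At stake is a declaration of feasibility on the approach criterion that would not stand if refusals were counted.

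**Working it through.** **Inputs from the article**
- Criterion 1: above 80%, denominator eligible patients (Outcomes).
- Criterion 2: above 20%, same denominator (Outcomes).
- Planned numbers: 200 eligible over 2 years, 100 randomized (Sample size).
- Provider refusal rate d, as a share of otherwise eligible infants: not given. Assumed range 5% to 20%.

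**The plan's own figures.** Sample size states that observed rates of 82.7% (n = 600) and 86.9% (n = 100) put the one-sided 95% lower limit at 80%. The exact (Clopper-Pearson) limit gives 82.74% and 86.89%, so both reproduce. The precision arithmetic is sound; the issue is only who is in the denominator.

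**Relation.** Let N be the otherwise eligible infants. Refusals remove dN, so the reported denominator is N(1 − d). If a is the reported rate, the numerator is aN(1 − d), and

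rate over all otherwise eligible infants = a × (1 − d).

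**Criterion 1 (approach)**

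| Reported rate | d = 5% | d = 10% | d = 15% | d = 20% |
|---|---|---|---|---|
| 85% | 80.8% | 76.5% | 72.3% | 68.0% |
| 90% | 85.5% | 81.0% | 76.5% | 72.0% |
| 100% | 95.0% | 90.0% | 85.0% | 80.0% |

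The corrected rate equals 80% at d = 1 − 0.80/a:
- a = 85%: 1 − 0.80/0.85 = 5.9%
- a = 90%: 1 − 0.80/0.90 = 11.1%
- a = 100%: 1 − 0.80/1.00 = 20%

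Beyond these values the verdict reverses.

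The same in counts: read literally, the 200 expected eligible infants are already net of refusals. With 180 of 200 approached (90%), 25 refusals on top give 180/225 = 80%, and d = 25/225 = 11.1%, as above.

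**Criterion 2 (enrollment).** The planned rate is 100/200 = 50%. With refusals added to the denominator:
- 10 refusals: 100/210 = 47.6%
- 20 refusals: 100/220 = 45.5%
- 40 refusals: 100/240 = 41.7%
- 100 refusals: 100/300 = 33.3%
- 300 refusals: 100/500 = 20%

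The bias has the same direction, but it would take 300 refusals to bring the planned rate down to the threshold.

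**The case against.** A provider opt-out is a usual safeguard, and the approach rate among infants who can actually be enrolled is a legitimate measure of how well the team reaches families. That stands. The opt-out itself is not at fault, only its use to define the denominator of a primary feasibility measure.

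The article also has other benchmarks. Sample size sets a screening target of 80% of all patients (n = 600), which would not lose refusals. The Discussion plans to compare infants who screened in with those who screened out. The study halts below 20 enrolled per year. These might expose a very large loss, but they do not change the rule in Outcomes by which feasibility is decided. The Sample size target concerns screening of all patients, whereas criterion 1 concerns approach among eligible ones.

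Tabulating reasons for exclusion can be left to a full protocol or analysis plan. The eligibility list and the feasibility definitions, however, are both fixed in this article, and their interaction follows from its text.

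Three stronger readings are tempting and are not supported:
- A reader might infer that the enrollment criterion would also be passed wrongly. On the planned figures it has wide slack.
- A reader might infer that a large share of infants will be lost to refusal. The article gives no refusal rate, so only the direction and the break-even values can be stated.
- A reader might infer that infants given a second routine SUP dose before they are reached certainly drop out of the denominator too. Inclusion criterion 5 and the site's standard practice make this possible, but the text does not say when eligibility is fixed. Table 1 allows screening and consent before the study starts, and mailers go out before delivery or surgery, so many infants may be identified early.

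**Conclusion.** The point holds for provider refusals. With any refusal at all, criteria 1 and 2 as written overstate the rates over otherwise eligible infants, by a factor of 1/(1 − d): 1.05 at d = 5%, 1.11 at 10% and 1.25 at 20%.

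The material effect is on criterion 1. A reported 85% or 90% passes, yet would fail once refusals exceed about 5.9% or 11.1% of otherwise eligible infants. Even a reported 100% allows no more than 20%. Because all four criteria must be met, this one can decide the overall result. Criterion 2 is unlikely to change verdict, provided enrollment comes near the planned 50%.

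The size rests entirely on d, for which 5% to 20% is an assumption. A similar loss through the one-dose SUP limit is possible but depends on when eligibility is fixed, which the article leaves open.

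**What to change.** Keep the provider opt-out as a bar to enrolling the individual infant. For criteria 1 and 2 only, define eligible as meeting all inclusion criteria and exclusions 1 to 10 when first screened. Setting the time at first screening, not at ICU admission, fits the criteria that rest on anticipated respiratory support or drug exposure.

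Count as eligible but not approached:
- infants whose provider declines;
- infants eligible at first screening who receive a second routine SUP dose before the family is approached.

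Report the number in each group separately, so that the approach rate among enrollable infants can still be read off.

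The cost is a change to the outcome definition, with no effect on the treatment of any infant or on the sample size. The remaining criteria must be checked, and the refusal recorded, at screening even when the provider declines; the article does not say whether this is already done. The reported feasibility rates may be lower.
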